### Intervention

The study design is a 24-week RCT to assess the efficacy of POWERS_*for*ID_ on weight loss and overall health status (target sample: n = 70). The primary aim of this study is to test the feasibility and efficacy of the POWERS_*for*ID_ intervention in obese adults with ID. With a moderate effect size of 0.62 and a two-sided alpha of 0.05, a sample size of 35 participants per group will achieve a power of 0.80. After consent, all participants complete baseline measures and are then randomized to one of two conditions: (1) POWERS_*for*ID_ intervention; or (2) control. De-identified patient demographic data were used to conduct simulation checks to ensure balanced group allocation and to determine a proper randomization protocol. Simulation checks accounted for age, race, and ethnicity. After the simulation checks, a simple randomization sequence was developed. Each individual randomization assignment was then sealed in an envelope. Participants have equal probabilities of randomization to the intervention or control group. When it is time to randomize a participant to either arm, the health coach opens the next envelope in the sequence to reveal the group assignment. Participants are recruited, enrolled, and randomized by the health coach; all other research staff have been blinded to randomization. Participants randomized to the control group receive usual care from the clinic and related clinic staff. In addition, during the 24-week intervention, control group participants complete assessments at baseline, and at weeks 6, 12, and 24. Upon completion of the study period, control group participants are provided educational materials from an online information and resource center specializing in health and disability, as well as the option to contact a toll-free number and speak with an information specialist for further advice on physical activity and nutrition.

Participants randomized to the intervention group receive access to the POWERS_*for*ID_ website and review the interface with the health coach. The participant and coach schedule an initial phone call to review strategies to improve physical activity and diet. Subsequent phone calls occur weekly until the 12th week of the intervention and biweekly during weeks 13–24. All participants visit the clinic at baseline and at weeks 6, 12, and 24. The study protocol is summarized in Fig. 2 (based on SPIRIT 2013 guidelines).

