### Outcomes

Outcome measures and timing of administration are listed in Table 2. Clinic visits include routine care, the HAP, and measurement of body weight and body composition (via waist circumference and bioelectrical impedance analysis). Blood samples for measurement of lipids and blood sugar are collected at baseline and week 24. Participants will be required to visit their medical provider at baseline and weeks 6, 12, and 24. During the visits, participants will receive medical supervision that mimics the routine care provided by the clinic. Routine care consists of measuring a patient’s blood pressure, 0_2_ saturation, urinalysis, height, weight, and waist circumference. Medical records will be accessed to collect the participant’s blood sample results. For the POWERS_*for*ID_ intervention clinicians will also measure body composition via bioelectrical impedance analysis and waist circumference. Standard procedures for assessing anthropometrics, such as removal of additional clothing items, measuring from between the lowest rib and iliac crest for waist circumference, will be utilized in line with standardized clinical procedures. The HAP is completed following completion of clinical measures and may be completed with assistance from a caregiver (if applicable) and/or the health coach.

**Table 2 Tab2:** Outcome measures, instruments, and time points

Measures	Instruments	Time point(s)
Adherence	Logs, enrollment metrics, tracking data	Daily
Demographics	Demographics	Baseline
Functional abilities	POWERS_*for*ID_ disability, health and function	Baseline
Body weight	Scale and bioelectrical impedance analysis of body composition	Clinically measured at baseline and weeks 6, 12, and 24
Physical activity behaviors	Physical Activity and Disability Scale; Barriers to Physical Activity and Disability Scale; Exercise Perception Scale; Self-Efficacy Related to Exercise for People with DD Scale	Baseline and weeks 6, 12, and 24
Physical activity	Physical activity points and steps (pedometer)	Daily
Barriers to PA	Barriers to Physical Activity and Disability Scale	Baseline, weekly, 24 weeks
Nutritional behaviors	Block Food Frequency Questionnaire; Fruit and Vegetable Self-Efficacy Scale; Fruits and Vegetables Outcomes Expectancy Scale; Barriers to Fruits and Vegetables Scale	Baseline and weeks 6, 12, and 24
Nutrition	Healthy eating points	Daily
Dietary barriers	POWERS_*for*ID_ dietary barriers	Baseline and weeks 6, 12, and 24

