### Data analysis

Data analysis is performed by a project coordinator and statistician who are blinded to the intervention group assignment. Participant attrition, session attendance, and instrument completion are recorded and analyzed using descriptive statistics. We hypothesize that by the end of the study, 70% of the participants will be retained, 70% will participate in all coaching sessions, and 100% will have completed at least 80% of the survey instruments at each data collection point. Data will be analyzed with mixed effects models to assess the effect of POWERS_*for*ID_ on participant outcomes. A mixed model is a generalization of the standard linear model that permits repeated measures data to exhibit correlation and non-constant variability over time. We will use each outcome as a time-varying dependent variable and group (POWERS_*for*ID_ vs. control) as main fixed effects. Baseline demographics will be entered as time-invariant covariates if baseline group differences are observed. Intercept will be modeled as random effects. We hypothesize that the trajectory slope of participant outcomes will be more favorable in the POWERS_*for*ID_ group compared to the control group, which will result in a significant GroupXTime interaction effect. We will analyze our data using both on-treatment and intent-to-treat approaches. Participants lost through attrition will be compared on demographic and prognostic variables to those who remain in the study to examine the sample representativeness and potential treatment bias.

Qualitative data analysis from the POWERS_*for*ID_ study results will address motivational interviewing applications, barriers, and successes of the intervention. We will perform thematic analysis using ATLAS.ti software. Thematic analysis is an iterative process that involves the researcher as the instrument for: (1) coding qualitative data; (2) cross-comparing codes for pattern identification; (3) grouping codes into broader themes; and (4) interpreting thematic relationships [31, 40]. We will also report on the level of data saturation achieved.

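### A slope test from a model whose only stated random effect is the intercept can exceed its 5% level when participants' true slopes differ: up to about 26% with four visits

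*Protocol article*

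**What the plan says.** The protocol article (Data analysis) applies mixed effects models to each outcome, with group as a fixed effect. On the random part it says only "Intercept will be modeled as random effects". The efficacy hypothesis is that the slope of the outcome trajectory is more favourable under the intervention, "which will result in a significant GroupXTime interaction effect". The same paragraph introduces mixed models with the general remark that such a model "permits repeated measures data to exhibit correlation and non-constant variability over time".

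Weight is "Clinically measured at baseline and weeks 6, 12, and 24" (Table 2), and the abstract gives the same times for waist circumference and percent body fat. Lipids are taken at baseline and week 24 only. For the questionnaires, the abstract and the Health Appraisal Profile section give baseline and weeks 12 and 24, while Table 2 adds week 6 for most of them.

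**The concern.** A random intercept with independent, equal-variance residuals lets participants differ in level but not in rate of change. In a weight-loss trial the rates are likely to differ: goals are individualised, and the Discussion describes participants who resist changes of routine, vary in comprehension or have competing medical problems. The model then counts each person's departure from the group slope as visit-to-visit noise. It averages that departure over all within-person degrees of freedom, although it acts entirely along the time axis. The estimated slope difference stays unbiased, but its standard error is too small.

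At stake is the only between-group efficacy effect that the section names. Its p-value would fall below 0.05 too often under no effect, and its confidence interval would be too narrow.

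**Working it through.** **The plan's own figures.** The article gives no type I error other than the nominal one: "With a moderate effect size of 0.62 and a two-sided alpha of 0.05". For power, the Intervention section then claims that "a sample size of 35 participants per group will achieve a power of 0.80". The simple two-sample calculation gives 0.62 × √(35/2) = 2.594; 2.594 − 1.960 = 0.634; power Φ(0.634) = 0.737 (0.725 with the t distribution). The stated 0.80 is therefore not reproduced unless an unstated gain from baseline or repeated measures was used. That is a separate matter, and power does not enter the calculation below.

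**Inputs from the article.** 35 per group; 1:1 allocation ("Participants have equal probabilities of randomization to the intervention or control group"); visits at weeks 0, 6, 12 and 24. Mean time is 10.5 weeks, so Sxx = 110.25 + 20.25 + 2.25 + 182.25 = 315.

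**Inputs assumed, because the article gives none.** s_b is the SD between participants of the true weekly slope, expressed as the SD of slope-driven 24-week change (24 × s_b). s_e is the SD of independent visit noise. Time is linear.

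**Formulae (balanced data, n per group, m visits).**
- True variance of the slope difference: (2/n)(s_b² + s_e²/Sxx).
- Variance reported by the random-intercept model: (2/n)(s_e² + s_b²·Sxx/(m−1))/Sxx.
- With q = s_b²·Sxx/s_e², true/reported variance is R = (1+q)/(1+q/(m−1)).
- Actual type I error = 2[1 − Φ(1.96/√R)].

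R cannot exceed m−1. With q = 0 it is 1, and the formula returns 5.0%.

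**Worked case, 3 kg and 2 kg.** q = (3/24)² × 315/4 = 1.23; R = 2.23/1.41 = 1.58; 1.96/1.258 = 1.558; type I error 11.9%.

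| SD of 24-week change / visit noise | q | Type I error, formula |
|---|---|---|
| 1 / 2 kg | 0.14 | 6.0% |
| 2 / 3 kg | 0.24 | 6.8% |
| 3 / 2 kg | 1.23 | 11.9% |
| 5 / 2 kg | 3.42 | 17.3% |
| 3 / 1 kg | 4.92 | 19.1% |
| 5 / 1 kg | 13.67 | 22.8% |
| slope variance dominant | → ∞ | 25.8% |

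**Other visit schedules.** With three visits R is at most 2, so the ceiling is 16.6%. With two visits R = (1+q)/(1+q) = 1, so there is no inflation.

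**Simulation check.** The random-intercept model was fitted by REML with 35 per group, 600 runs per scenario (Monte Carlo standard error about 1 to 2 percentage points).

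| Scenario | Complete data | 30% dropout |
|---|---|---|
| No slope variation, noise 2 kg | 5.0% | 6.3% |
| 1 / 2 kg | 7.8% | 7.7% |
| 3 / 2 kg | 12.7% | 14.3% |
| 5 / 2 kg | 16.5% | 19.7% |
| 5 / 1 kg | 22.7% | 24.7% |

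A two-sample t-test on each participant's fitted slope, which carries the between-person slope variation, rejected in 3.9% to 5.2% of 2000 runs in each of seven scenarios.

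**If time is categorical and the random intercept is kept.** In the 3/2, 5/2 and 5/1 kg scenarios the 3-df interaction test rejected in 5.7%, 7.5% and 9.2% of runs. The week-24 contrast rejected in 12.2%, 16.8% and 21.3%.

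**The case against.** The strongest reply is that the size of the problem is not in the document. No slope variance, residual SD or within-person correlation is given, and with little slope variation the error is close to nominal (6.0% at 1 kg and 2 kg). That stands: 12% to 23% is a result for assumed SDs, not a property of the plan.

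Second, an article may leave the residual structure and standard-error method to a fuller plan, and equal correlation between visits follows only if residuals are independent with equal variance. That also stands as a condition. But the article does not leave the random part open: it fixes the intercept, names nothing else, and pairs it with a slope hypothesis. The remark on non-constant variability reads as a general description of mixed models. It neither supplies a structure nor amounts to a plain contradiction.

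Third, time coding is not stated. A 3-df test would be inflated less. The hypothesis speaks of a slope, however, and a week-24 contrast under a random intercept is affected almost as much.

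Several stronger readings are tempting and not supported:
- A reader might take Group × Time as the declared primary test or success criterion. The section states a hypothesis for outcomes in general and names neither a primary outcome nor a success rule.
- A reader might extend the weight figures to every repeated outcome. No questionnaire was examined, and a noisy scale with little slope variation would show little inflation.
- Since "Subsequent phone calls occur weekly until the 12th week of the intervention and biweekly during weeks 13" to 24, a reader might conclude that a straight line fits badly. The change in call frequency makes curvature possible, but nothing in the article shows it.
- That a slope does not estimate the week-24 difference is not an error, because the article never names that difference as its target.

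**Conclusion.** The point holds conditionally. With the intercept as the only random effect, the slope test is anti-conservative whenever true slopes differ between participants and residuals are independent. For outcomes at weeks 0, 6, 12 and 24 the actual two-sided error lies between 5% and about 26%. For weight it is about 12% to 23% if the SD of true 24-week change is 3 to 5 kg and visit noise is 1 to 2 kg, and about 6% at 1 kg and 2 kg. The ceiling is about 17% for outcomes with three visits. Lipids are not affected.

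This should be fixed before analysis. It does not show that the trial's error rate is any particular figure, because the ratio that decides it is unknown.

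**What to change.** For outcomes with three or more visits, replace "Intercept will be modeled as random effects" with: *Intercept and slope for time are random effects with an unstructured covariance, and tests use small-sample degrees of freedom.* This keeps the slope hypothesis.

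Alternatively, treat visit as categorical, use an unstructured within-participant covariance, and state the week-24 group contrast as the effect to be tested. This changes the quantity estimated, so it should be a deliberate choice. For four visits the matrix has 4 × 5/2 = 10 parameters, which is affordable with 70 participants, or with the 49 left at the article's 70% retention (0.70 × 70). Categorical visits with the random intercept alone do not cure the week-24 contrast.

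Neither replacement model was fitted in the check above. The evidence that the level is restored comes from the t-test on individual slopes.

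The change is to wording only and needs no new data or visits. Confidence intervals become wider, but correct, and power is somewhat lower.

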## Discussion

The POWERS_*for*ID_ intervention aims to adapt and assess a novel telehealth interface that has been proven effective for other populations with disabilities. Overall, there are few publications demonstrating weight loss in adults with ID [41]. Recently, Ptomey et al. [42] reported clinically significant weight loss for adults with intellectual disability utilizing conventional diet recommendations (500–700 kcal/day restriction) in conjunction with monthly counseling sessions. Greater weight loss was observed in participants recommended a stoplight-based diet plus counseling. These findings support the effectiveness of stoplight-based information delivery, where “red” signifies foods and actions to avoid and “green” signifies foods and actions to be pursued.

After pilot assessment, the POWERS_*for*ID_ website and nutrition material were redesigned utilizing the stoplight theme. Ptomey et al. [20] also previously reported successful food logging and video chat sessions for adolescents with ID through use of a tablet computer, indicating technology may be effective with individuals with ID. To our knowledge, no interventions targeting weight management for individuals with ID utilizing an online platform and motivational interviewing techniques have been tested with this population. POWERS_*for*ID_ is the first intervention addressing diet and physical activity habits in adults with ID through an online interface and coaching calls. If the POWERS_*for*ID_ system is demonstrated to be efficacious, it could be incorporated into clinical health settings that have a similar specialty in providing healthcare services to adults with ID as the clinic involved in this study. A home-based telehealth approach would be helpful in assisting a population that is at greater risk of obesity and other chronic health conditions.

Preliminary findings from this study have identified several challenges. First, adults with ID may be unwilling to alter familiar routines or make changes to diet and physical activity habits. Food is often used as a reward in the ID population, and it is a challenge replacing unhealthy food choices (e.g. candy, cookies, chips, etc.) with healthier alternatives. Second, intervention materials have been adapted to the cognitive abilities of the target population, but concepts such as nutrition labels and serving size are difficult for some individuals to comprehend. Phone sessions and clinic visits will provide an opportunity for the coach to identify the individual’s abilities. With the assistance of the research team, the coach and participant can identify health-related behaviors that are effective for the individual and new solutions can be archived for future use. Third, individuals with ID and/or their caregivers may have other medical issues or stressors that increase difficulty of sustained weight loss. Coaches must be respectful of extraneous circumstances and develop solutions that avoid overburdening family members. For these reasons, the POWERS_*for*ID_ interface and the protocol’s time commitment has been simplified as much as possible. Preliminary feedback indicated the POWERS_*for*ID_ carbohydrate food log plus system interface were overly complex. Any health tracking requires additional effort on the part of the participant, although efforts have been made to reduce overall workload for the participant. Individuals enrolling in the POWERS_*for*ID_ study indicate a desire to be “healthier” and the goal of the system is to encourage health-related behaviors.

Notwithstanding the potential findings from this study, POWERS_*for*ID_ does provide a structure for carefully monitoring and managing key health behaviors in adults with ID. The system has the potential to raise their level of awareness about their own health behaviors as well as awareness of their caregiver and/or direct support staff when appropriate. Individuals with ID are in need of additional accessible health promotion, and the POWERS_*for*ID_ project aims to address this need. Final results from the intervention study are expected in 2018.

### Trial status

This trial is currently ongoing and open to recruitment. Recruitment began 20 September 2016.
